### Inclusion and exclusion criteria

Provided below are the detailed criteria used to assess the eligibility of patients, individual biopsy slides or WSIs for inclusion in this study.

#### Inclusion criterion

Patients who underwent a prostate core needle biopsy were eligible.

#### Exclusion criteria

Clinical information:Patients with either slides or associated pathology information unavailable.Slides lacking identifiers (IDs) preventing linkage to the pathology data.Slides with identical IDs preventing unambiguous linkage to the pathology data.Slides with mismatching GS and ISUP grade information.Slides with mismatching information concerning malignancy and GS or ISUP grade (eg, indicated benign but a GS is provided).Slides with partial or erroneous GS reporting (eg, <6, 4+0 or 1+1, etc).Staining and slide preparation:Samples not containing prostate tissue, for example, bladder biopsies, testicular biopsies.Samples not stained with H&E (eg, IHC stains).Initial cuts of tissue blocks deemed unsuitable by the pathologist for providing a diagnosis and requiring a recut.Empty biopsy slides with no tissue on the glass.Slide integrity and annotation:Slides with pen mark annotations that cover a vast amount of the tissue, obscuring the underlying morphology.Slides with pen mark annotations conflicting with the pathology diagnosis (eg, there exists a pen mark annotation on the slide, but the slide is diagnosed as benign or vice versa). This only applies to the STHLM3 cohort, where the pen mark annotation process is known to be consistent for all samples (see Stockholm3 (STHLM3) in online supplemental appendix 2).Slides with pen mark annotations that result in the majority of the tissue being out of focus during scanning.Slide digitisation:Earlier scans of the same slide on the same scanner instrument, assuming the latest WSI represents a successful rescanning due to, for example, earlier focus issues.Corrupt WSI files which cannot be accessed with OpenSlide^37^ or OpenPhi.^38^

### Data partitions

#### Requirements for data partition

We established a number of requirements to guide the inclusion, exclusion and partitioning of data into development, tuning and validation sets to account for several sources of potential bias in the training and validation of the model. We followed available guidelines and criteria for balanced and representative data partitions^32 34 39 40^ and arrived at the following set of requirements:

Representative sample selection: Ensure the data are representative of the diversity encountered in clinical practice by including multisite cohorts with variations in scanning equipment (eg, vendors, models, image formats), biopsy preparation (eg, staining, tissue cutting), morphological heterogeneity (eg, different GSs and rare cancer subtypes) and patient demographics.Representative sample size: Include a sufficiently large sample for development and validation to increase the probability of generalisability in the larger population.Mitigate overfitting due to observer bias: Alleviate the possibility of overfitting or ‘over tweaking’ of the model, which may be caused by excessive refinement of the model design aimed at maximising cross-validation performance in development data, since that can jeopardise generalisation outside the development cohorts. The issue can be mitigated by additional (external) tuning data cohorts serving as a less biased performance indicator during model development. It should be further ensured that the tuning cohorts are independent of model training (eg, criteria for early stopping of model training should be assessed only on the development data).Ensure independence of specimens between data partitions: Each data partition (development, tuning, internal or external validation sets) should be independent of the others with no overlap of biopsies or patients.Ensure independence of the sample preparation process between data partitions: Sample external cohorts such that there is no overlap with respect to the clinical laboratories that prepared these cohorts and the development cohorts.Ensure independence of the digitisation process between data partitions: Sample external cohorts such that there is no overlap with respect to the scanning device used for these cohorts and the development cohorts.

#### Predefined data partitions

The process of splitting the data cohorts into development, tuning, and internal and external validation sets was conducted adhering to the requirements for data partitions and is described below (see figure 1 for an overview). The characteristics of the data cohorts included in this study are described in detail in online supplemental appendix 2.

The development set was sampled from the following cohorts: Capio S:t Göran Hospital (STG), Radboud University Medical Center (RUMC), Stavanger University Hospital (SUH) and Stockholm3 (STHLM3). From the RUMC, STHLM3 and SUH cohorts, the patients who were not allocated to tuning or validation sets (see below) were assigned to the development set (approximately 80% of patients). Given the limited size and skewed grade distribution of the STG cohort, it was fully allocated into the development set. The development set covers several clinical laboratories and scanner devices as well as a large degree of variation in tissue morphology and the clinical characteristics of patients, in part due to the largest cohort, STHLM3, originating from a population-based screening trial (Requirements 1–2). Each of the development cohorts was further split into 10 cross-validation folds by randomly allocating patients to folds, stratified by the maximum slide level ISUP grade of each patient.

The tuning set was sampled from the following cohorts: Karolinska University Hospital (KUH-1), RUMC and STHLM3. The entire KUH-1 cohort was assigned to tuning and represents a fully external cohort relative to the development set (ie, different patients, laboratory and scanner). This set also corresponds to the European external validation cohort of the PANDA challenge.^17^ The subsets of the RUMC and STHLM3 cohorts assigned to the tuning set represent internal data relative to the development set (ie, different patients but the same laboratories and scanners) and correspond to the PANDA public test sets in Kaggle (ie, the PANDA tuning sets). The tuning sets allow for evaluating the effects of model design changes on data that is independent of the development set, direct comparison with state-of-the-art models from PANDA, and in the case of KUH-1, assessing the generalisation performance of the model prior to design freeze (ie, performance on data coming from different patients, laboratories and scanners compared with the development data) (Requirement 3). A subset of slides belonging to the PANDA Swedish tuning set was allocated to the internal validation set for reasons related to patient stratification and the inclusion of specific subsets of interest in the internal validation (see below).

The internal validation set was sampled from the following cohorts: RUMC, STHLM3 and SUH, consisting of patients who were not part of the development or tuning sets but whose biopsies were obtained from the same clinical laboratories and scanned with the same scanners as the development and tuning set samples. The STHLM3 internal validation set includes the following subsets, supplemented with randomly sampled patients to achieve a total 20% fraction of patients assigned to tuning and validation: ImageBase,^36^ Swedish private test set in Kaggle (ie, PANDA Swedish internal validation set),^17^ PNI multiobserver validation set^41^ and rare morphological subtypes set.^42^ Including these samples as subsets of the internal validation set will facilitate (internal) comparisons with results obtained in the papers referenced in the preceding sentence. The SUH internal validation set includes the following subsets, supplemented with randomly sampled patients to achieve a 20% fraction of patients assigned to validation: all patients (n=25) with multiple recuts of their biopsy tissue blocks, and patients (n=81) corresponding to a random selection of 119 slides stratified on ISUP grade (to be rescanned repeatedly over time for an AI temporal stability study). The STHLM3 subsets allocated into the internal validation set were selected based on being particularly valuable for the evaluation phase of the study, while the SUH subsets will be used as validation sets in upcoming follow-up studies involving the AI model developed here, hence cannot be assigned to the development set. The RUMC internal validation set includes the RUMC private test set in Kaggle (ie, PANDA RUMC internal validation set),^17^ supplemented with randomly sampled patients to achieve a total 20% fraction of patients assigned to tuning and validation.

External validation cohorts are fully external relative to the development set (no overlap with respect to patients, laboratory or scanner) or partly external (no overlap with respect to patients or laboratory, but digitisation performed using a scanner that is also present in the development set). Fully external validation set cohorts include Aichi Medical University (AMU), Aarhus University Hospital (AUH), KUH morphological subtypes (KUH-2), Mehiläinen Länsi-Pohja (MLP), Medical University of Lodz (MUL), Synlab Switzerland (SCH), Synlab Finland (SFI), Synlab France (SFR), Spear Prostate Biopsy 2020 (SPROB20), University Hospital Cologne (UKK), Hospital Wiener Neustadt (WNS). Partly external validation set cohorts include: Aquesta Uropathology morphological subtypes (AQ), partially scanned on a scanner present in the development set and partially scanned on an external scanner. The external nature of the validation set cohorts fulfils Requirements 4–6.

All data splits were performed on patient level, that is, all slides and resulting WSIs from a given patient were allocated to the same data partition in order to avoid information leakage between development and validation sets. If a patient was biopsied on several occasions, all biopsies were included and allocated together. Any samples lacking patient identifiers were assigned to development data to avoid the risk of slides from any patients ending up in both development and evaluation cohorts.

Subsets of the slides included in this study have been scanned multiple times. If the same slide had been rescanned multiple times on the same individual scanner (ie, the same physical device), we only kept the WSI with the latest scanning date, assuming the rescanning was due to, for example, initially poor focus or other scanning issues. Subsets of the STG, STHLM3 and MUL cohorts were rescanned with multiple different scanners (see table 1). To avoid biasing the evaluation towards these slides that appear in the dataset multiple times, we will only include one WSI per slide in the validation sets. For STHLM3, we will randomly select one WSI for each slide to be evaluated, and for MUL, we will use WSIs from the Grundium Ocus40 scanner, excluding those on the Philips UFS scanner. This ensures that the MUL cohort remains entirely external relative to the development data, considering that the STHLM3 cohort was partly digitised on the same Philips UFS instrument. The repeated scans will, however, be used during AI model development as an augmentation technique (except for the Grundium Ocus40 which is kept as an external scanner for validation), and for a separate cross-scanner reproducibility analysis (see section Statistical analyses).

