The validation phase will employ a blinded approach, wherein neither the pathologists nor the AI model have access to each other’s assessments. The validation cohorts consist of samples representing a range of heterogeneous clinical settings and were collected from patients not included in the development or tuning cohorts. They are categorised as internal (scanner and laboratory included in the development set), partly external (scanner included in the development set) or fully external (neither scanner nor laboratory included in the development set) depending on the slide scanners and clinical laboratories involved. Internal validation can be expected to provide an optimistic estimate of the diagnostic performance of the AI model in the absence of laboratory or scanner variation. The generalisation performance of the model will ultimately be evaluated on the external validation cohorts, which avoids any optimistic bias. The design also allows for additional validation cohorts to be added at any point after the development phase.

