	RUMC	Radboud University Medical Center, Nijmegen, The Netherlands	January 2019–December 2019	3DHISTECH	Pannoramic Scan ll	N/A	20× (0.4861 µm)	.tiff	5275
	STG*	Department of Immunology, Genetics, and Pathology, Uppsala University, Uppsala, Sweden	September 2018–October 2018	Hamamatsu	C13210	000058	20× (0.4405 µm)	.ndpi	74
		Department of Immunology, Genetics, and Pathology, Uppsala University, Uppsala, Sweden	October 2018	Hamamatsu	C13210	000044	20× (0.4409 µm)	.ndpi	67
		SciLifeLab, Uppsala, Sweden	December 2018	Aperio	AT2 DX	RUD-D10971	20× (0.5032 µm)	.svs	247
	KUH-1	Department of Pathology, Karolinska University Hospital, Solna, Sweden	July 2019–August 2019	Hamamatsu	NanoZoomer S360 C13220-01	000077	20× (0.4604 µm)	.ndpi	330
								.tiff	330
External and partly external validation cohorts	AMU	Aichi Medical University, Nagakute, Japan	January 2023–December 2023	Hamamatsu	C13210	000218	40× (0.2211 µm)	.ndpi	73
	AQ	Department of Medical Epidemiology and Biostatistics, Karolinska Institutet, Solna, Sweden	October 2019–June 2020	Philips	IntelliSite UFS	FMT0047	40× (0.2500 µm)	.isyntax	58
		Department of Medical Epidemiology and Biostatistics, Karolinska Institutet, Solna, Sweden	January 2024–February 2024	Grundium	Ocus40	MGU-00 003–0 00 184	40× (0.2505 µm)	.svs	78
	AUH	Department of Pathology, Aarhus University Hospital, Aarhus, Denmark	November 2019–June 2020	Hamamatsu	NanoZoomer 2.0-HT C9600-12	1Z0209	20× (0.4545 µm)	.ndpi	102
	KUH-2	Department of Pathology, Karolinska University Hospital, Solna, Sweden	July 2022	Aperio	AT2 DX	SS7033	20× (0.5032 µm)	.svs	146
	MLP	Finnish Institute of Molecular Medicine, Helsinki, Finland	October 2019–March 2020	3DHISTECH	Pannoramic 250 Flash III	01702	40× (0.2427 µm)	.mrxs	1964
	MUL*	Department of Medical Epidemiology and Biostatistics, Karolinska Institutet, Solna, Sweden	December 2019–January 2020	Philips	IntelliSite UFS	FMT0047	40× (0.2500 µm)	.isyntax	503
		Department of Medical Epidemiology and Biostatistics, Karolinska Institutet, Solna, Sweden	January 2023–March 2023	Grundium	Ocus40	MGU-00 003–0 00 184	40× (0.2505 µm)	.svs	1945
	SCH & SFI & SFR	Synlab Italia srl, Monza, Italy	June 2022–February 2023	Philips	IntelliSite UFS	N/A	40× (0.2500 µm)	.isyntax	3486
	SPROB20	Uppsala University Hospital, Uppsala, Sweden	2020	Hamamatsu	NanoZoomer S360 C13210	N/A	40× (0.2204 µm)	.tif	2570
	UKK	Institute of Pathology, University Hospital Cologne, Cologne, Germany	N/A	Hamamatsu	NanoZoomer S360	N/A	40× (0.2305 µm)	.ome.tiff	50

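### The STHLM3 scan draw can put an unseen scanner into internal validation, and Table 1 does not verify that SPROB20's scanner is external

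*Protocol article*

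**What the plan says.** Study design sets three classes. For the first it says "They are categorised as internal (scanner and laboratory included in the development set"; partly external means that only the scanner is in the development set, and fully external means neither. Predefined data partitions repeats the reference point: "External validation cohorts are fully external relative to the development set (no overlap with respect to patients, laboratory or scanner". It also says that internal validation samples were scanned on the scanners used for development and tuning. Scanner identity is taken at the level of the device, as in "rescanned multiple times on the same individual scanner (ie, the same physical device".

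On repeated scans, the same section says "For STHLM3, we will randomly select one WSI for each slide to be evaluated". It then keeps the Grundium Ocus40 out of development as an external scanner for validation, and it uses only Ocus40 scans for MUL so that MUL stays fully external.

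The list of fully external cohorts begins "Fully external validation set cohorts include Aichi Medical University (AMU), Aarhus University Hospital (AUH), KUH morphological subtypes (KUH-2" and goes on to include SPROB20. Table 1 gives the SPROB20 scanner as "NanoZoomer S360 C13210", at Uppsala University Hospital, with no serial number. The STG cohort is wholly development data. Part of it was scanned at "Department of Immunology, Genetics, and Pathology, Uppsala University, Uppsala, Sweden" on two Hamamatsu C13210 devices, serials 000058 and 000044.

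On Karolinska, the section states "The entire KUH-1 cohort was assigned to tuning".

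**The concern.** The study is meant to show generalisation to unseen laboratories and digitisation platforms, so the cohort labels carry the interpretation. Internal validation is described as the optimistic estimate, free of laboratory or scanner variation, against which external results are read. If internal validation contains images from a withheld scanner, that contrast is no longer clean. If a cohort is called fully external when its scanner cannot be told apart from a development device, the reader is given an assurance that the table does not back.

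**Working it through.** No sample size or power figure is at issue. The check compares labels with definitions and uses simple arithmetic on Table 1.

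**STHLM3 draw**

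- Internal, by Study design: scanner and laboratory both in development.
- Ocus40, by Predefined data partitions: not in development.
- Draw for STHLM3: random, with no scanner excluded.
- Table 1: 2289 STHLM3 scans on the Ocus40, under the serial also listed for MUL and for 78 AQ slides. The article treats that device as external for both of those cohorts.

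A drawn Ocus40 scan comes from a seen laboratory on an unseen scanner. It fits none of the three classes.

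Size:
- Share of native-format STHLM3 scans: 2289 / (5726 + 3667 + 17,973 + 32,078 + 2289) = 2289 / 61,733 = 3.7%.
- Illustration: sensitivity analysis A gives 287 slides scanned on five scanners. If all are in the set drawn from and each scan is equally likely, 287 / 5 = 57.4, about 57 slides.
- Range under assumptions. Take 20% of 36,848 slides, about 7370, as the set drawn from. The 20% in the article is of patients and includes tuning, so this is approximate. Let each Ocus40 slide have 2 to 5 scans.
  - Ocus40 scans spread evenly: 0.2 × 2289 = 457.8 slides; divided by 5 and by 2 this gives about 92 to 229 (1.2% to 3.1%).
  - All Ocus40 scans in that set: 2289 / 5 to 2289 / 2, about 458 to 1145 (6.2% to 15.5%).

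**SPROB20**

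The model entry joins a name and a code that Table 1 elsewhere keeps apart: S360 goes with C13220-01 (KUH-1), and C13210-01 goes with S60 (SUH).

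Pixel sizes at 40×, with 20× values halved:

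| Entry | µm |
|---|---|
| SPROB20 | 0.2204 |
| STG 000058 (C13210) | 0.4405 / 2 = 0.22025 |
| STG 000044 (C13210) | 0.4409 / 2 = 0.22045 |
| SUH (S60 C13210-01) | 0.2199 |
| AMU (C13210) | 0.2211 |
| KUH-1 (S360 C13220-01) | 0.4604 / 2 = 0.2302 |
| UKK, WNS (S360) | 0.2305 |

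SPROB20 lies inside the C13210 range (0.2199 to 0.2211) and well below the S360 values (0.2302 to 0.2305). That points to a model. It cannot single out a device, because C13210 scanners in Norway and Japan give nearly the same value.

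**KUH-2**

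- Reference set for external: development. KUH-1 is tuning only.
- Scanners: KUH-2 was scanned on Aperio AT2 DX SS7033; the development AT2 DX is RUD-D10971.
- The label therefore satisfies the definition.
- What remains: Table 1 lists the same Karolinska pathology department for KUH-1 and KUH-2, and Study design sets hyperparameters and thresholds on development and tuning cohorts. In Table 4, KUH-2 supplies 146 of 146 + 78 = 224 fully external morphology slides (65%).

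**The case against.** On STHLM3, the Figure 1 legend describes internal data as sharing laboratory and/or scanner with development, which would admit Ocus40 scans by laboratory. That is true of the legend. It conflicts with the definition in Study design, however, and read literally it would turn the AQ slides scanned on the development Philips device into internal data, while Predefined data partitions calls them partly external. It adds a further definition and does not settle the matter.

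On SPROB20, the article says that N/A marks metadata that were not available, and the cohort is open repository data whose details sit in an appendix not shown here. The named Uppsala institutions differ, as do the scanning years (2020 against 2018) and the magnification. All of this stands, and it is why the point is limited to lack of verification. Missing serials alone would not matter: the Synlab cohorts, UKK and WNS also lack them, but their scanning sites appear nowhere in development. The stake is also bounded. The two STG devices contributed 74 + 67 = 141 scans, and a shared device would only make SPROB20 partly external, a class that already exists.

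A reader might go further and infer that KUH-2 is mislabelled because its hospital was seen in tuning. The article measures external status against development only, so this does not follow. The rule that tuning data join training covers only the cribriform and perineural invasion models, for which KUH-2 is not evaluated.

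A reader might also infer that the fully external claim as a whole is overstated, or that a quarter of the external evidence is in doubt. The STHLM3 draw touches internal data only. SPROB20 is 2570 of 10,386 fully external images (24.7%, leaving AQ out), but it is analysed at patient level, and the article describes validation against cohort-specific reference standards. That share is not a share of any stated estimate.

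**Conclusion.** The point holds in a limited form. The STHLM3 draw contradicts the definition of internal validation, and the sections must be reconciled. Its extent is unknown from the article; the figure of about 57 slides and the wider ranges rest on the assumptions stated with them. The consequence is a blurred internal-external contrast, with no inflation of external results. No effect on a performance estimate can be shown from the article.

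For SPROB20, Table 1 does not establish that the scanner is external. It does not establish overlap either, and the laboratory is external in any case.

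KUH-2 is correctly labelled. Its link to the tuning cohort merits at most a sentence of disclosure.

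**What to change.** 1. Restrict the STHLM3 internal draw to scanners present in development. Use the Ocus40 scans only in sensitivity analysis A, or report them in a separate row for same laboratory, unseen scanner. Align the Figure 1 legend with the definition in Study design.
2. Read the SPROB20 file metadata or ask the data provider, and correct the model entry in Table 1. Unless the device is shown to differ from serials 000058 and 000044, label SPROB20 as scanner not verified external; if it proves to be shared, label it partly external.
3. Keep the KUH-2 label. At most, note in subgroup analysis D that it shares a pathology department with tuning cohort KUH-1.

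The cost is a filter on the draw, one metadata query and a few lines of text. The locked model is unaffected and no patient moves between partitions.

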### Statistical analyses

#### Overview of statistical analyses

Primary analysis: Diagnosis and Gleason scoringInternal and external validation against the original cohort-specific reference standardSubgroup analysesEvaluate performance across different age groups.Evaluate performance on systematic versus targeted biopsies.Evaluate performance on non-treated patients versus patients treated for benign prostatic hyperplasia (BPH) prior to biopsy.Evaluate performance on morphological subtypes.Evaluate performance on cases requiring versus not requiring IHC staining.Evaluate performance compared with the current state-of-the-art AI systems.Sensitivity analysesCross-scanner consistency analyses.Compare the AI system versus individual pathologist panel members.Internal and external validation against uniform reference standard by the lead pathologist.Blinded reassessment of slides with marked errors.Secondary analysis: Cancer extent predictionInternal and external validation against the original cohort-specific reference standards.Subgroup analysesEvaluate performance across different age groups.Evaluate performance on systematic versus targeted biopsies.Evaluate performance on non-treated patients vs patients treated for BPH prior to biopsySensitivity analysesCross-scanner consistency analyses.Secondary analysis: Cribriform cancer detection

Internal and external validation against the original cohort-specific reference standards.Subgroup analysesEvaluate performance across different age groups.Evaluate performance on systematic versus targeted biopsies.Evaluate performance on non-treated patients versus patients treated for BPH prior to biopsy.Sensitivity analyses

Cross-scanner consistency analysesCompare the AI system versus individual pathologist panel members.Reassessment excluding borderline slides.

Secondary analysis: PNI detectionInternal and external validation against the original cohort-specific reference standards.Subgroup analysesEvaluate performance across different age groups.Evaluate performance on systematic versus targeted biopsies.Evaluate performance on non-treated patients versus patients treated for BPH prior to biopsy.Sensitivity analysesCross-scanner consistency analysesCompare the AI system versus individual pathologist panel members.Reassessment excluding borderline slides.Exploratory analysesEvaluate visualisations of the AI output.Evaluate the impact of tissue segmentation algorithmsEvaluate end-to-end versus transfer-learning-based models.Evaluate the impact of physical colour calibration.

